#### AEs include

(1) presence of urinary crystals.(2) occurrence of acute kidney injury (AKI) as defined by KDIGO criteria.(3) clinical or laboratory signs of unexpected hemolytic anemia (e.g., sudden hemoglobin drop combined with elevated indirect bilirubin), specifically to monitor for undetected G6PD deficiency.

#### SAEs include

(1) death,(2) life-threatening conditions.(3) prolongation of hospital stay.(4) persistent or significant disability.(5) congenital anomalies or birth defects.

#### Treatment discontinuation criteria

Study drug infusion must be discontinued immediately for any of the following events. Emergency unblinding may be performed if deemed necessary by the attending physician:

(1) new-onset AKI meeting KDIGO Stage 2 or 3 (serum creatinine ≥ 2.0 × baseline or urine output < 0.5 mL/kg/h for ≥ 12 h) judged as potentially related to vitamin C-associated oxalate nephropathy.(2) microscopic urinalysis showing abundant calcium oxalate crystals (≥50 per high-power field) with acute creatinine rise.(3) clinical or laboratory evidence of hemolytic anemia (sudden hemoglobin drop, elevated indirect bilirubin, hemoglobinuria).(4) confirmed hypoglycemia (<3.9 mmol/L) after excluding glucometer interference by venous blood gas confirmation.(5) any SAE judged as possibly or definitely related to the study drug.

Both AEs and SAEs will be evaluated at 8:00 a.m. every day. Investigators are required to promptly assess the aforementioned adverse events. If the investigator determines that an abnormal laboratory result is clinically significant and not part of the clinical condition, it should be recorded as an adverse event and report to the PI of each research site. Once confirmed, the intervention should be discontinued immediately and proper medication should be taken.

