### Eligibility criteria

#### Inclusion criteria

Participants must meet the following criteria:

Age ≥ 18 years;Time from onset to enrollment is less than 7 days;Meets the diagnostic criteria for SAP per the 2012 Atlanta Guidelines, defined by persistent organ failure (modified Marshall score of 2 or higher lasting more than 48 h). Confirmation of the 48-h persistence must be completed within 7 days of disease onset.

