#### Exclusion criteria

Participants who meet any of the following criteria will be excluded from the study:

SAP caused by tumors or ERCP;Pregnancy or breastfeeding;Allergy to vitamin C;Use of other experimental drugs during the study period;Pre-existing chronic organ failure affecting the heart, liver, lung, or kidney prior to admission, defined as: chronic cardiovascular dysfunction requiring long-term mechanical hemodynamic support or inotropic drugs; chronic obstructive pulmonary disease requiring home oxygen therapy; chronic liver failure classified as Child-Pugh grade C; chronic kidney disease defined by eGFR less than 60 mL/min/1.73 m^2^ (CKD-EPI 2021). Baseline creatinine is based on stable outpatient values from the past 6 months; if unavailable, exclusion relies on a documented history of chronic kidney disease rather than an acute admission creatinine.Immunosuppressive states, including malignant tumors, post-transplant conditions, long-term use of immunosuppressor (for at least 1 month before enrollment), or AIDS;Refuse to sign the informed consent form;Weight > 100 kg;Presence of urinary tract stones identified during the current admission (including symptomatic clinical events or incidental findings on baseline abdominal imaging).Known personal or strong family medical history of G6PD deficiency (routine laboratory screening is not required prior to enrollment).

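### The mandatory renal stopping rule is limited to new-onset AKI, so worsening of AKI already present at entry, when possibly drug-related, is not clearly a mandatory stop (minor)

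*Protocol article*

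**What the plan says.** Five events require immediate discontinuation of study drug (Protocol article, Treatment discontinuation criteria). The first is "new-onset AKI meeting KDIGO Stage 2 or 3", given as creatinine at least 2.0 times baseline or urine output below 0.5 mL/kg/h for at least 12 h, and it must be "judged as potentially related to vitamin C-associated oxalate nephropathy". The second is "microscopic urinalysis showing abundant calcium oxalate crystals" (50 or more per high-power field) together with an acute creatinine rise. The fifth is "any SAE judged as possibly or definitely related to the study drug". The closing paragraph adds a stop, once confirmed, for an abnormal laboratory result that the investigator considers "clinically significant and not part of the clinical condition".

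On who can enter, the Inclusion criteria require "persistent organ failure (modified Marshall score of 2 or higher lasting more than 48 h" and do not carve out the kidney. The Exclusion criteria remove chronic kidney disease only, and there the article says "Baseline creatinine is based on stable outpatient values from the past 6 months". Table 1 records CRRT from Day 0, and Data collection and management names renal impairment among the organ failures to be recorded.

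**The concern.** The qualifier new-onset suits a patient who enters with working kidneys. It fits poorly in a population where acute renal failure can be part of the entry condition. In such a patient the event of interest is deterioration from an already abnormal state, and no listed criterion names it.

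At stake is the timing and consistency of stopping at 500 mg/kg/day for 7 days. The article itself treats oxalate injury to the kidney as a main hazard. Two centers reading the same sentence differently could stop at different points for the same clinical course.

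**Working it through.** No figure in the plan bears on this point, so the check is a reading of the text.

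**Step 1. Can a patient in AKI enter?** Yes. Organ failure is required, renal failure is not excluded unless chronic, and CRRT is recorded at Day 0.

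**Step 2. What does the first criterion cover?** New-onset can be read strictly (the AKI itself must be new) or broadly (the patient newly enters the combined category of stage 2 or 3). All rows assume that the event is judged potentially related.

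| State at Day 0 | Event | Strict reading | Broad reading |
|---|---|---|---|
| No AKI | Reaches stage 2 or 3 | Stop | Stop |
| Stage 1, not on RRT | Progresses to stage 2 or 3 | Not covered | Stop |
| Stage 2, not on RRT | Progresses to stage 3 | Not covered | Not covered |
| Stage 3 or on RRT | Any worsening | Not covered | Not covered |

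A stage 2 entrant is already in the combined category at Day 0, so a move to stage 3 is not its onset. The urine-output limb does not help in an entrant who was already below 0.5 mL/kg/h for 12 h: it is met before the first dose and cannot signal deterioration.

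**Step 3. What else could stop the drug in rows two and three?**

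- *Second criterion.* It has no new-onset condition and needs no causality judgement. It does need heavy crystalluria with a creatinine rise, so it serves patients who pass urine and misses worsening without that finding.
- *Fifth criterion.* Its causality bar is low, but the event must first be an SAE. The SAE list includes death, life-threatening conditions and "prolongation of hospital stay". Worsening renal failure may qualify, though possibly later than a change of stage would show.
- *Closing paragraph.* KDIGO-defined AKI of any stage is on the AE list, and events are assessed daily. The stop applies to results outside the clinical condition. That is harder to assert when renal failure was part of the condition at entry, and it is a higher bar than potentially related.
- *Emergency unblinding* (Randomization and blinding). Urinary crystals or unexplained AKI lead to unblinding and to joint management by the site and study-wide principal investigators. They may well stop the drug, but the text does not require it.
- *Dose adjustment* (Intervention). This is left to clinical judgement.

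**Step 4. What remains?** A patient in stage 1 or 2 AKI at Day 0, not on RRT, whose stage rises and in whom oxalate nephropathy is thought possible. There is no qualifying crystal finding, no related SAE yet, and no confident judgement that the change lies outside the pancreatitis. The stage 2 part of this group is uncovered on both readings, and the stage 1 part on the strict reading only. The article gives no figure for how many entrants are in AKI, so no size can be put on the group.

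**Step 5. The reference creatinine.** The first criterion uses baseline without pointing anywhere. The only definition in the article is the outpatient value in the Exclusion criteria, and carrying it over is the natural reading.

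**The case against.** The strongest case against is that the safety net is wider than the first criterion alone. AKI of any stage is an AE, assessed daily, and the closing paragraph already stops the drug when a change is attributed to something other than the pancreatitis. Worsening beyond stage 2 will often become an SAE, and the fifth criterion then needs only a possible link. Unexplained AKI leads to emergency unblinding, so the two principal investigators decide knowing the allocation. Limiting the first criterion to new-onset events is also defensible: AKI present before the first dose cannot be caused by the drug, and pancreatitis-driven worsening is expected. Most of this stands, and it is why the point is minor. It does not remove the gap, because none of these routes makes a stage-based, potentially related worsening a mandatory stop.

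A reader might infer that patients in AKI at entry have no stopping protection. The provisions in step 3 contradict that.

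A reader might also infer that the stop line could float because baseline might mean the Day 0 creatinine. No text states that reading, and the one definition given points to outpatient values. A substitute for patients without an outpatient value is detail that a condensed article can leave to the full protocol.

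**Conclusion.** The point holds as a minor safety improvement. For an entrant in AKI and not on RRT, worsening judged only potentially related to oxalate nephropathy is not clearly a mandatory stop. From stage 2 it lies outside the first criterion on either reading; from stage 1 it depends on the reading. Other provisions cover part of the gap, the remaining group is narrow, and its size is unknown. The conclusion rests on the published article and assumes that the full protocol words the criterion in the same way.

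Because the article keeps the dose unchanged on CRRT, a reader might infer that the main failing concerns those patients. The document does not support that. The unchanged dose is a stated and reasoned choice, and no figure shows how many such patients enter or how they fare. A worsening rule based on stage cannot reach patients on RRT or already at stage 3. Whether they need a trigger of their own is a question for the sponsor's clinicians and the DMC.

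**What to change.** Reword the first criterion to *new-onset or worsening AKI: newly reaching KDIGO stage 2 or 3, or, in a patient with AKI at Day 0 who is not on RRT, a rise in KDIGO stage from Day 0*. Keep the relatedness clause as it stands. Add a cross-reference so that baseline means the outpatient creatinine defined in the Exclusion criteria.

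The cost is a short rewording, a cross-reference and one derived Day 0 field (KDIGO stage and RRT status). Renal function and CRRT are already recorded at Day 0, so no new procedure is needed. It does require an amendment at centers that already have ethics approval. With 34 of 238 patients recruited at the date given under Sample size, the change could still reach at most 238 − 34 = 204 patients (204/238 = 86%). The downside is that some infusions may stop for worsening caused by the pancreatitis itself; the retained relatedness clause limits this.

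### The discontinuation section pairs a list of narrowed stopping events with a broader closing instruction to stop, and does not say how the two fit together

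*Protocol article*

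**What the plan says.** Three places in the protocol article bear on when the study infusion ends.

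- **Treatment discontinuation criteria, numbered list.** The lead-in is "Study drug infusion must be discontinued immediately for any of the following events". Item 1 is "new-onset AKI meeting KDIGO Stage 2 or 3", further limited to cases thought possibly due to oxalate nephropathy. Item 2 is "abundant calcium oxalate crystals (≥50 per high-power field) with acute creatinine rise". Item 3 is evidence of hemolytic anemia. Item 4 is hypoglycemia below 3.9 mmol/L, confirmed after glucometer interference has been excluded. Item 5 is "any SAE judged as possibly or definitely related to the study drug".
- **Treatment discontinuation criteria, closing paragraph.** AEs and SAEs are reviewed daily, and investigators must assess promptly the adverse events already mentioned. The trigger described next is: "If the investigator determines that an abnormal laboratory result is clinically significant and not part of the clinical condition". Such a result is recorded as an AE and reported to the site's principal investigator. The paragraph ends: "Once confirmed, the intervention should be discontinued immediately and proper medication should be taken".
- **Intervention.** For complications such as hyperoxaluria, oxalate deposition or urate stones, the dose is to be altered according to clinical need, and discontinuation is an option in severe cases.

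The AE definitions matter too. Under AEs include, the first item is simply "presence of urinary crystals", with no count, and the second is any acute kidney injury by KDIGO criteria, with no minimum stage.

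**The concern.** The list has been narrowed with care: stage, crystal count plus creatinine rise, exclusion of a measurement artefact, relatedness. The closing sentence has none of these conditions, yet it also orders an immediate stop. A centre that works from the list and a centre that works from the closing paragraph can treat the same patient differently, and both can show that they followed the protocol.

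The intervention under test is 7 days of continuous infusion at eight hospitals, so a stopping rule that can be read in more than one way bears directly on the treatment received. It also bears on trial conduct. The Monitoring section starts retraining when a centre's deviation rate exceeds 10% and has the DMC look at deviation patterns across centres. A stop that one paragraph requires and another does not cannot be classified consistently as adherence or deviation. The per-protocol analysis named in Statistical methods meets the same difficulty.

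**Working it through.** The point is textual. No figure in the article depends on it, so there is none to reproduce. The check is to take concrete cases and see what each text tells a site to do.

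The closing sentence has two main readings. In reading A, it refers to the laboratory AE described immediately before it, which is the nearest antecedent. In reading B, it refers back to the adverse events that investigators were told to assess, which can include those defined under AEs include.

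| Case | Numbered list | Closing sentence, reading A | Closing sentence, reading B |
|---|---|---|---|
| KDIGO Stage 1 kidney injury | No instruction to stop, unless a related SAE | Stop, if it passes the investigator's two-part judgement | Stop |
| Stage 2 or 3 kidney injury not thought oxalate-related | No instruction to stop, unless a related SAE | Stop, if it passes | Stop |
| Crystals below 50 per field, or without creatinine rise | No instruction to stop, unless a related SAE | Stop, if it passes | Stop |
| Other non-serious laboratory AE, unrelated to the drug | No instruction to stop, unless it meets item 3 or 4 | Stop, if it passes | Not reached, unless it is one of the defined AEs |
| Unrelated SAE with no such laboratory result and no other listed event | No instruction to stop | Not reached | Not reached, unless it is also one of the defined AEs |

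The two-part judgement is that the result is clinically significant and lies outside the clinical condition.

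1. **Reading A.** In each of the first four rows the list and the closing sentence can give different answers. The stage in item 1, and the count and creatinine condition in item 2, no longer decide whether the drug stops. The last two rows together produce an inversion: a non-serious laboratory AE unrelated to the drug could end treatment, while an unrelated SAE would not.
2. **Reading B.** The first three rows become stops without even the two-part judgement, because the AE definitions carry no count and no minimum stage. The list's renal qualifiers are undercut again.
3. **Intervention section.** Take a patient with oxalate deposition who also meets item 2. The list requires an immediate stop. The Intervention section calls for a dose change and makes stopping an option in severe cases. This conflict does not depend on how the closing sentence is read.

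The article gives no frequency for any of these cases, no split by arm and no indication of which text a centre would follow. The number of patients affected therefore cannot be calculated.

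**The case against.** The strongest reply is that the list does not claim to be complete. Nothing in it says that these are the only grounds for stopping; item 3 has no numeric cut-off and item 5 is a general category. A list of mandatory stops followed by a further stop on the investigator's judgement is additive, not a strict contradiction. That is correct, and a reader who infers a closed list goes further than the text. But the additive reading does not remove the problem, because the added stop absorbs the laboratory qualifiers that the list sets out.

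Second, the requirement that the result lie outside the clinical condition, together with clinical significance, reporting and confirmation, is a real filter and works as a partial attribution test. This stands, and the table allows for it. It is still not a test of drug-relatedness: a change caused by a concomitant drug is also outside the condition.

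Third, the closing sentence might mean only confirmation of an event already on the list. There would then be one rule within that section. The wording does not settle on this reading, and the difference from the Intervention section would remain.

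Fourth, the Monitoring section provides training, daily eCRF recording of interruptions and their causes, and DMC review across centres. These help to detect divergence, but they cannot settle which paragraph governs.

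A reader might also infer a mismatch on hemolysis, since AEs include speaks of "sudden hemoglobin drop combined with elevated indirect bilirubin" while item 3 separates its signs by commas. The documents do not support this. The phrase under AEs include is given as an example, and in item 3 the operative condition is evidence of hemolytic anemia. A fall in hemoglobin from bleeding alone does not meet it.

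**Conclusion.** The point holds as a conflict of wording. One section contains stopping instructions of different breadth, the closing sentence has an unclear referent, and the Intervention section adds a different instruction for oxalate and stone complications. Centres can differ in who stays on the infusion while each complies with the text. What is affected is exposure, the classification of deviations and the per-protocol set. Intention-to-treat membership is unchanged.

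A reader might go on to infer a definite loss of effect or power, or that the vitamin C arm would be stopped more often than placebo outside the listed events. Either may happen, but the documents give no stopping rates, no timing and no information by arm. Any figure would rest wholly on assumption, and a loss applied to the whole arm would overstate a problem that arises only where centres diverge. No size is therefore claimed.

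The conclusion assumes only that sites act on the printed text. It takes no view on which stopping rule is clinically right.

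**What to change.** The sponsor and DMC should reconcile Intervention, AEs include and Treatment discontinuation criteria so that one unambiguous set of discontinuation criteria applies. The text should state what the closing sentence refers to and how the closing paragraph relates to the numbered list. The clinical content of those criteria is for the sponsor and DMC to decide. The existing eCRF, which already captures interruptions and their causes, should also record which criterion led to each permanent stop.

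The cost is a short protocol amendment, one eCRF field and a note in the site training. The article reports 34 patients recruited at the lead centre with the other centres still being activated, so most sites could start under the reconciled wording if it is issued soon.

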### Monitoring

All investigators (physicians, UDPNs, nurses, pharmacists, and data managers) must complete standardized training and pass a competency assessment before center activation. Study medication originates from a single production batch across all eight centers to ensure pharmacological consistency.

Adherence to the infusion protocol is monitored daily. Study nurses record infusion start time, rate, interruptions, and interruption causes in the electronic CRF. Cumulative interruptions <2 h per 24-h cycle are considered acceptable and interruptions ≥2 h are classified as protocol deviations, with the patient retained in the ITT analysis.

Each center’s PI reviews deviations quarterly and submits summary reports to the DMC. If the deviation rate for any procedure exceeds 10% at a given center, targeted retraining is initiated. The DMC reviews cross-center deviation patterns regularly. Systematic inter-center differences trigger focused quality assurance measures.

A combined approach of central statistical monitoring and periodic on-site monitoring is employed. Concomitant therapies (fluid resuscitation, antibiotics, nutritional support) follow standardized SAP management guidelines across all centers, and all such therapies are prospectively recorded for potential statistical adjustment.

### Expected results

We anticipate that the continuous administration of HDIVC at 500 mg/kg/day for 7 days will result in an improvement in the primary outcome of OSFD within the first 14 days among SAP patients compared to the placebo group. HDIVC is expected to effectively neutralize excessive ROS and halt the progression of MODS. We also expect that HDIVC will lead to improvements in ICU all-cause mortality, early SAP inflammatory markers, organ function scores, fluid retention, disease severity scores, pancreatic necrosis, ICU length of stay, and hospitalization costs.

## Discussion

The evidence for IV vitamin C in critical illness has evolved substantially. The CITRIS-ALI trial (*n* = 167) found no reduction in SOFA scores in sepsis-associated ARDS (22), and the LOVIT trial (*n* = 872) reported that vitamin C (50 mg/kg every 6 h for up to 96 h) increased the risk of death or persistent organ dysfunction in adults with sepsis receiving vasopressor therapy (RR 1.21, 95% CI 1.04–1.40) (23). Meta-analyses have been mixed: Liang et al. (24) found no mortality benefit, whereas Lee et al. (25) reported a mortality reduction with monotherapy. These discordant results suggest that vitamin C efficacy depends critically on disease context, dose, timing, method of administration (bolus injection or micropump infusion), and drug types that affect solution pH (ascorbic acid or sodium ascorbate)—none of the existing large trials targeted SAP specifically. The negative results of CITRIS-ALI trial and LOVIT trial may be attributable, in part, to the use of bolus injection and ascorbic acid (pH ~ 5.5–6.5), which can aggravate acidosis in critically ill patients. In the present trial, we administer sodium ascorbate—a pH-neutral formulation (pH ~ 7.0–7.4)—via continuous micropump infusion, which provides stable steady-state concentrations, avoids bolus-related adverse effects, and may improve tolerability and efficacy. The dose (500 mg/kg/d) is substantially higher than those used in LOVIT trial and our prior SAP trial, selected via pharmacokinetic modeling to achieve higher plasma concentrations required for antioxidant and vasopressor-synthesis effects.

HDIVC represents a promising adjunctive therapy for SAP by targeting oxidative stress and systemic inflammation. If proven effective, the study may provide evidence to support future guidelines. However, several challenges still remain. Patient heterogeneity and variability in disease course may influence treatment response. Patients >100 kg are excluded because weight-based dosing in predominantly adipose excess could yield a disproportionately high drug load. The 50 g/d cap is consistent with established safety limits (21), though this limits generalizability to obese SAP patients. Inter-center variability in supportive care is inevitable in a pragmatic eight-center trial. We mitigate this through centralized training, protocol-driven management, including center as a random intercept, and prospectively recording concomitant therapies. Timely enrollment is critical to capture the early inflammatory phase, but in clinical practice, delays in diagnosis or transfer may limit early intervention. To avoid this as far as possible, we set a 7-day cutoff from the onset of the disease during which vitamin C may exert therapeutic effect on SAP. But the 7-day enrollment window requires organ failure documentation by Day 5 to meet the Atlanta SAP criteria, which may delay or preclude enrollment.

